## Abstract

**Background:**

Mental disorders are highly prevalent, and mental health problems often start in childhood or adolescence. However, barriers to care, such as low mental health literacy and stigma, increase the risk of developing mental disorders. The abilities to recognize, talk about and seek help when mental health problems occur are important processes to overcome such barriers. The school-based prevention program “Talking mental health” (TMH) aims to reduce stigma among children in elementary schools and their families by increasing mental health literacy and help-seeking behavior.

**Methods:**

In this study, the “Talking mental health” (TMH) prevention program is evaluated using a cluster-randomized design, comparing an intervention group with a waitlist control group. The primary outcomes are mental health literacy, stigma and help-seeking behavior. Measurement takes place pre and post, as well as at a six-week follow-up. The sample size aims for 35 school classes with approximately 525 parents and children. The study also examines the effects of an additional parent training on children’s and parents’ mental health.

**Discussion:**

If effective, this study provides a validated prevention program to promote mental health in elementary schools, potentially allowing wider implementation. This could help families access existing support structures at an early stage, therefore preventing the chronic progression of mental health problems. The methodological and practical challenges of the study are discussed, as well as general challenges of school-based prevention efforts.

**Clinical trial registration:**

https://drks.de/search/en/trial/DRKS00035171, identifier DRKS00035171.

## Introduction

1

Both parents and children express uncertainty about how to recognize mental health problems and where to find support (Reardon et al., 2017; Tharaldsen et al., 2017). Mental health literacy is an important health competence and is defined as knowledge and beliefs about mental disorders that facilitate their recognition, management or prevention (Jorm et al., 1997). The importance of mental health literacy is highlighted by the high prevalence of mental disorders in the general population. In Germany, where this study takes place, 42.6% of people suffer from a mental disorder at least once in their life (lifetime prevalence in Germany; Jacobi et al., 2004). Children and adolescents are also affected. Half of mental disorders have their onset around the age of 14 (Kessler et al., 2005). The median age of manifestation for anxiety and impulse-control disorders is even earlier, at 11 years (Kessler et al., 2005). With respect to prevalence rates in the UK, 20% of all children struggle with mental health problems by the time they finished elementary school (Morrison Gutman et al., 2015). Across Europe, the prevalence of mental disorders among 5-18-year-olds was found to be 15.5% (Sacco et al., 2024). In Germany, prevalence rates of 17.6% were reported (Barkmann and Schulte-Markwort, 2012). Additionally, the coronavirus pandemic has seemingly exacerbated the situation, especially for children (Ravens-Sieberer et al., 2022).

Furthermore, mental disorders during adolescence are associated with numerous negative long-term outcomes, such as unfavorable educational burdens, financial difficulties, poor social functioning and increased risk of problematic substance use (e.g., Shaw et al., 2012; Asselmann et al., 2018). Even though mental disorders are highly prevalent and associated with negative consequences, only a minority of those affected receive professional treatment (Hintzpeter et al., 2015). The waiting times for outpatient psychotherapy are long (in Germany, approximately 20 weeks from initial contact to the start of treatment), and children and adolescents face even longer waiting times than older patients do (Singer et al., 2022). Moreover, children and adolescents are largely dependent on their parents in seeking help. Preventive intervention in settings that reach as many children as possible, such as schools, has an important role in changing low early access to care. Students themselves expressed a desire for more proactive education and understanding of mental health in schools (Marinucci et al., 2022). Given the early onset of mental disorders, this study protocol presents an approach to mental disorder prevention with the aim of increasing mental health literacy and help-seeking behavior in elementary schools using age-appropriate materials. The following sections highlight the barriers that young people face in seeking help and emphasize the crucial role of mental health literacy and stigma in this process.

A systematic review examined the most frequently mentioned barriers preventing young people from seeking help (Radez et al., 2021). The two most cited categories were individual and social factors (Radez et al., 2021). Individual factors included young people not knowing whether their problem was severe enough (e.g., Guterman et al., 2010) and not knowing where to find help (e.g., Sheffield et al., 2004). Overall, young people were found to have little knowledge of available help services for mental disorders (Tharaldsen et al., 2017). Indeed, seeking help was often seen as a weakness (e.g., Tharaldsen et al., 2017), and young people believed that they could handle it on their own (e.g., Sheffield et al., 2004; Rickwood et al., 2005) or hoped that it would go away if they did not talk about it (e.g., Guterman et al., 2010). Among social factors, the most commonly reported barrier was perceived stigma (e.g., Gronholm et al., 2017), accompanied by fear of losing one’s status within a peer group (e.g., Tharaldsen et al., 2017) or being insulted and ostracized (Gronholm et al., 2017). Experiencing stigma for mental health problems is not only a fear but also a reality for children and adolescents (Kaushik et al., 2016). It is therefore not surprising that perceived public stigma was associated with lower intentions to seek help among adolescents (Nearchou et al., 2018).

The process model by Rickwood and colleagues suggests that four steps are required to seek help for mental health problems: (1) awareness and appraisal of the problem (emotional competence); (2) telling others that there is a problem (expressing symptoms and need for support); (3) the source of help must be available; and (4) willingness to open up to the source of help (Rickwood et al., 2005). Emotional competence in step one is defined as the ability to recognize, describe, understand and functionally manage emotions and has been associated with increased help-seeking behavior (Rickwood et al., 2005). Each of these four steps can be affected by perceived barriers (Rickwood et al., 2005). Therefore, reducing such barriers, promoting mental health literacy and emotional competence are key to increasing help-seeking behavior. For example, studies have shown that fewer perceived barriers (such as stigma) are associated with more formal and informal help-seeking behavior (Sheffield et al., 2004; Zuaboni et al., 2021). Mental health literacy was also found to be associated with increased help-seeking behavior (e.g., Gorczynski et al., 2017). Additionally, findings highlight an inverse relationship between mental health literacy and stigma: greater knowledge of mental disorders was associated with more positive attitudes toward help-seeking behavior (Sheffield et al., 2004).

While the literature agrees that mental health literacy and stigma play crucial roles in the process of considering help-seeking behavior, there is disagreement regarding whether these are independent factors or whether stigma acts as a mediating factor. Several models suggest that mental health literacy, or knowledge about mental health disorders, leads to more positive (i.e., less stigmatizing) attitudes, which in turn facilitate help-seeking behavior (Sheffield et al., 2004; Jung et al., 2017; Ma et al., 2023b). However, some studies found a direct effect of mental health literacy on help-seeking behavior without mediation through stigma (Sheffield et al., 2004; Jung et al., 2017), whereas others demonstrated that reducing stigma through increased mental health literacy can increase help-seeking behavior (Kim, 2023; Yang et al., 2024).

In summary, interventions that aim to improve mental health should focus on reducing stigma among young people and their families while at the same time increasing mental health literacy (Xu et al., 2018). Children and adolescents should be equipped with the knowledge and confidence to identify mental health problems, talk about them, access appropriate support, and help their peers effectively. Parents should also be informed about when and where to seek help for their children’s mental health problems and how to discuss these issues openly. Social support has been shown to be an important factor in young people’s help-seeking behavior, independent of mental health literacy and stigma reduction (Rickwood et al., 2005; Jung et al., 2017; Yang et al., 2024). Therefore, interventions should not only target children but also include their parents.

A recent review of randomized controlled trials testing school-based interventions to address mental health literacy and mental health stigma found an overall moderate level of evidence (Ma et al., 2023a). However, they identified only two randomized controlled trials in elementary schools (Pitre et al., 2007; Link et al., 2020), one of which included children in grade 6 (age 11.5; Link et al., 2020). This highlights the urgent need for evidence-based interventions for children under 10 years of age. Furthermore, a review by the same authors revealed no strong evidence for the effectiveness of mental health literacy interventions on help-seeking behavior (Ma et al., 2023b). On the basis of this review, the authors expressed the need for practical and targeted help-seeking content in school-based mental health literacy interventions if the aim is to increase help-seeking behavior (Ma et al., 2023b). In conclusion, this meta-analysis highlighted the positive effects of mental health literacy interventions in elementary schools on increased mental health literacy. However, only studies with children aged 10 years and over were included in the analysis. In contrast, the effects of mental health literacy interventions on stigma reduction and help-seeking behavior are less clear across studies (Ma et al., 2023b). The available studies show that there is an urgent need for evidence-based interventions in elementary schools that address not only mental health literacy but also help-seeking behavior and stigma.

The Anna Freud National Center’s prevention program “Talking mental health” (TMH) is one of the few such intervention programs addressing both mental health literacy and help-seeking behavior, which is also aimed at elementary school children aged 8–10 years (Sharples et al., 2017). Although the program has been widely implemented in the UK, it has not been extensively evaluated. An initial non-control group survey revealed that the training was very well received and that the children wanted to talk more about their feelings after the training (Sharples et al., 2017). The culturally adapted and tailored version for German-speaking countries, carried out by college students, will be fully evaluated as part of this research project.

Despite the positive impacts mentioned above, increasing mental health literacy does not directly reduce existing symptoms or disability (e.g., Jorm et al., 1997). Therefore, prevention programs require complimentary and targeted interventions to alleviate psychological symptoms in children and parents under stress. Parent training programs offer a cost-effective solution, as parental factors have been found to play a crucial role in the development of mental health problems in children (e.g., Yap et al., 2014). Evidence suggests that parenting skills training (Emotion focused skills training for parents; EFST-P; Dolhanty et al., 2022) leads to a reduction in both internalizing and externalizing symptoms in children (Ansar et al., 2022; Zahl-Olsen et al., 2023). In addition, immediately after the training and at follow-ups 4, 8 and 12 months later, parental self-efficacy and emotion regulation were strengthened, and psychological distress decreased in both parents and children (Ansar et al., 2024). Emotion focused skills training for parents (EFST-P) focuses on developing the following key skills: (1) validating children’s feelings, (2) increasing motivation, (3) apologizing, when necessary, and (4) setting appropriate boundaries for children (Dolhanty et al., 2022). In this study, all children receive the universal prevention program “Talking mental health” (TMH), and families with stress are also offered Emotion focused skills training for parents (EFST-P).

This research project investigates whether the school-based prevention program “Talking mental health” (TMH) can increase mental health literacy and help-seeking behavior while reducing the stigma of mental disorders. The primary aim of the prevention project is to improve children’s knowledge and attitudes toward managing difficult emotions. Parents are supported to talk to their children about their feelings and, if necessary, to access appropriate support services. In addition, the effects on college students implementing and being trained in the program are examined.

We expect that children who have completed the TMH program (compared to those in the waitlist control group) will show improved knowledge and skills in managing mental health problems and difficult emotions (increased mental health literacy; Hypothesis 1a), greater willingness to talk about their difficult feelings (increased intentional help-seeking behavior, Hypothesis 1b), increased actual help-seeking behavior (Hypothesis 1c), and reduced stigmatization of mental health problems (Hypothesis 1d). We expect these effects to be present both 1 week after the intervention and at least 6 weeks later. We expect that in the intervention group, an increase in mental health literacy will lead to a decrease in stigma, which in turn will cause an increase in help-seeking behavior (Hypothesis 1e).

Additionally, we expect that parents of children who completed the prevention program (compared with parents in the waitlist control group) will show increased help-seeking behavior for their children (Hypothesis 2a) and reduced stigmatization of mental health problems (Hypothesis 2b).

College students trained in and implementing the TMH program should show less stigmatization toward others than should college students in the control group (Hypothesis 3).

Finally, we expect parents who participate in the parent training program (Emotion focused skills training; EFST-P) and their children to demonstrate improved mental health after the conclusion of the program (Hypothesis 4a). This effect is achieved by increasing parents’ self-efficacy (Hypothesis 4b) and mentalization skills (Hypothesis 4c).

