### Statistical analysis

2.8

Data will be analyzed using the intention-to-treat approach. Multiple imputation will be used to impute missing values. We will analyze and report on attrition. We will check for possible correlations between our variables, primary and secondary outcomes, as well as sociodemographics, and dropout at different time points. Additionally, we will report the reasons given by parents or children for withdrawal. The main analysis is a multilevel analysis due to the nested data structure (children in school classes). Both inter- and intraindividual differences and changes are analyzed. Demographic variables will be included in the data analysis model to control for group differences at baseline. In addition, we will examine a possible mediating effect of increased mental health literacy on increased help-seeking behavior through reduced stigma using multilevel mediation analysis. In addition, we will use correlational analyses as well as chi-squared tests, *t*-tests, Mann–Whitney-U-tests and *F*-tests for group comparisons and comparisons across time points. A significance level of *α* = 0.05 will be used. To validate the newly constructed mental health literacy scale, exploratory factor analysis (EFA) will be conducted, and the comparability of the three vignettes will be checked using ANOVAs. Qualitative data will be analyzed using Mayring’s content analysis using both deductive and inductive approaches (Mayring, 2015). On the one hand, the responses will be matched (deductively) to a pre-established coding scheme to indicate the extent to which the mental health problem is understood by the participating children, and the appropriateness of the help offered by the child. The children’s responses will be grouped blindly by two independent assessors. In the case of discrepancies, the scores will be discussed. On the other hand, categories will be formed (inductively) from the answers to gain more precise insight into the content of the children’s answers.

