In our study, we primarily relied on self-reports. In this young age group, such reports may be influenced by social desirability or other response biases (Soneson et al., 2025; Wang and Zang, 2025). Mental health stigma (Kaushik et al., 2016) or concerns regarding data security (Soneson et al., 2025) may prevent children from openly reporting whether they are seeking help or have mental health difficulties. Similar issues, including stigmatization and shame, have also been described in the context of self-reported bullying assessments (Furlong et al., 2010). In accordance with the recommendations by Wang and Zang (2025), we used neutral wording and avoided leading questions. Prior to the interview, we informed the children that their answers would be treated as strictly confidential and recorded using a number–letter code instead of their names. We also reminded them that there were no right or wrong answers. We did not include social desirability detection items or validity screening items, which should be considered in future research (Cornell et al., 2012; Wang and Zang, 2025).

In addition, only schools in the Heidelberg area are included in this first evaluation study (convenience sampling method). The socioeconomic status in Heidelberg is above German average. Therefore, we consider the influence of socioeconomic status and migration background in our evaluation. It should be noted that, so far, 12 of the 28 schools contacted have expressed interest in participating in the study. Possible differences between participating and non-participating schools will be examined and reported after data collection in order to identify possible biases. When interpreting the findings, it is important to note that the results may not be representative or generalizable. This study should therefore be understood as an initial evaluation in the German-speaking context. Future research should implement the intervention in more rural areas and different countries.

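### As stated, the mediation hypothesis H1e takes non-randomised literacy change as its exposure, so it can show association but not that the programme works through literacy and stigma

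*Protocol article*

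**What the plan says.** In the Introduction, H1a to H1d are between-arm hypotheses about "children who have completed the TMH program (compared to those in the waitlist control group"). H1e changes the frame: "in the intervention group, an increase in mental health literacy will lead to a decrease in stigma, which in turn will cause an increase" (the final increase being in help-seeking). The exposure is a gain in literacy, the mediator is stigma, the outcome is help-seeking, and the wording is causal.

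Statistical analysis (2.8) plans to examine "a possible mediating effect of increased mental health literacy on increased help-seeking behavior through reduced stigma using multilevel mediation analysis". It does not give the arm a role in that model, and it does not limit the model to the intervention group. It also says, of the analysis in general, that "Both inter- and intraindividual differences and changes are analyzed". The only adjustment named there is for demographic variables.

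Table 1 shows that children report literacy, stigma and help-seeking at each of t1, t2 and t3. The Discussion warns that in this age group "such reports may be influenced by social desirability or other response biases", and states that no items to detect social desirability or invalid answers were included.

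**The concern.** Schools are randomised; a child's gain in literacy is not. Children who gain more may differ from their classmates in ability, engagement, home support or manner of answering, and any of these could also move stigma and help-seeking scores. If the exposure is literacy gain, no link in the stated chain rests on the allocation, although a randomised waitlist arm is available.

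The Introduction itself says that the literature disagrees on whether stigma lies between literacy and help-seeking. A significant H1e could be published as the programme's mechanism when it shows only that three child-reported scales move together. One route to this is in the document: a common response style across the scales, conceded in the Discussion and not addressed by demographic adjustment.

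**Working it through.** **Plan's own figure.** 35 classes × 15 children = 525, as stated. No sample size, effect or power is given for H1e. An even split gives 525 / 2 ≈ 262 children in the intervention arm. This is an assumption, because schools are allocated by coin toss without blocking.

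**Illustration with no causal path.** Assume a shared style gives correlation 0.3 between each pair of scales, standardised and scored so that higher is favourable.
- Literacy to stigma: a = 0.3; SE = √(0.91 / 260) = 0.0592.
- Stigma to help-seeking given literacy: b = (0.3 − 0.09) / (1 − 0.09) = 0.231. Explained variance is 2 × 0.231 × 0.3 = 0.138, so SE = √(0.862 / (0.91 × 259)) = 0.0605.
- Indirect effect: ab = 0.069.
- Sobel SE = √(0.3² × 0.0605² + 0.231² × 0.0592²) = 0.0227; z = 3.05, p = 0.002, before clustering.

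**Dependence on the assumption.** Simulation with no causal path, 15 children per class, intraclass correlation 0.05, class effects removed, two-sided 0.05, 1,000 runs per cell. Entries are false-positive mediation by joint significance of the two paths / by Sobel test. All inputs except class size are assumed.

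| Correlation | 12 classes | 18 classes | 24 classes |
|---|---|---|---|
| 0 | 0.2% / 0.0% | 0.2% / 0.0% | 0.2% / 0.0% |
| 0.10 | 5.5% / 0.9% | 10.8% / 3.0% | 17.3% / 5.4% |
| 0.20 | 45.8% / 22.5% | 67.7% / 47.6% | 84.0% / 68.6% |
| 0.30 | 82.1% / 72.5% | 95.6% / 93.5% | 99.4% / 98.9% |

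These rates apply to levels, or to changes when style varies by occasion. If style is a constant additive component for each child, it drops out of post minus pre. With 18 classes and simple change scores, the rate was then 0.0% at correlation 0.2 and 0.1% at 0.4 (joint significance).

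**What naming the arm achieves.** 36 classes, arm effect tested on class means, serial chain arm → literacy → stigma → help-seeking, correlations 0.1 / 0.2 / 0.3:
- no true arm effect: falsely positive in 1.2% / 5.3% / 4.6%;
- the programme raises literacy by 0.5 SD but there is no onward chain: 29.6% / 95.9% / 98.9%.

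Randomisation thus protects only the first path. These runs had no t1 adjustment and no t2-to-t3 ordering, so they do not show how far those steps would help.

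**Choice of outcome.** H1e does not say which help-seeking measure it means. The AHSQ asks about the past 6 months, about 26 weeks. The Discussion puts t3 at least 6 weeks after t1. At that minimum, about 20 of the 26 weeks precede the programme, and help sought then cannot result from a later fall in stigma. The GHSQ asks about intentions and has no such window.

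**The case against.** The strongest reply is that H1e is a sentence in the Introduction, while the analysis section gives one line on mediation and an article may leave the specification to a fuller plan. This stands against one inference a reader might draw, that half the sample is certainly dropped and the arm certainly plays no part. The one-arm restriction appears only in the hypothesis, and that phrase could merely say where a literacy gain is expected. It does not rescue the exposure, because the analysis section also starts the chain at literacy.

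A reader might also infer that the randomised evidence on the mediators is lost. It is not: H1a and H1d already test literacy and stigma against the waitlist. H1e adds the onward links, which are non-randomised under any model.

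Nor do the documents say that all three variables will be taken from one occasion; with three assessments, a lagged model remains open. H1e is worded in changes, where a stable style largely cancels, and the sentence on differences between and within children is general and does not assign levels to the mediation model. One common correlation is also a simplification. The literacy vignettes include open questions whose answers are grouped blindly by two assessors, actual help-seeking is a tick-list, and the stigma scale has reverse-coded items. The authors disclose the bias and describe neutral wording and assurances of confidentiality. These points limit the size of the bias. They do not make literacy gain a randomised exposure.

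Finally, the mediation is introduced as an additional look at a possible effect. That lowers the stakes, but H1e itself is written as a causal expectation.

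**Conclusion.** The point holds in limited form. As stated, the mediation analysis can establish association among child-reported literacy, stigma and help-seeking. It cannot establish that the programme works through them, and the causal wording goes beyond the design. This rests on the stated exposure, not on any simulated figure.

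The size of the response-style problem cannot be fixed from the documents. It ranges from almost nothing (stable style, pure change scores) to a false-positive rate above 90% (18 classes, correlation 0.3, levels or occasion-varying style). The correlation, intraclass correlation and arm size are all assumed. A reader might infer that a spurious mediation is near certain, or that the same associations must appear in the control group; the documents support neither. The between-arm comparisons in H1a to H1d are untouched.

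**What to change.** - Fit the mediation in both arms with randomised arm as exposure, literacy and stigma at t2 as mediators and help-seeking at t3 as outcome. Adjust each for its t1 value and respect clustering, bearing in mind that schools are the units allocated.
- Use intentional help-seeking (GHSQ) as the main mediation outcome, because of the AHSQ recall window.
- Report arm-to-mediator paths as randomised effects. Report literacy-to-stigma and stigma-to-help-seeking paths as associations under a stated assumption of no unmeasured confounding, with a sensitivity analysis. This part is essential, since naming the arm does not protect those paths.
- Reword H1e so that it no longer claims that one change causes the next.

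The cost is analysis text. No new measurements are needed: Trial status (3.1) reports 30 classes collected and 6 more planned, all on the existing schedule. The price is more parameters, a wider interval for the indirect effect, and a result that stays exploratory.
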